#### Data collection

The course of the study and the details regarding measurement times for relevant data/questionnaires are presented in online supplemental table. Patients will be managed according to standard practice for the follow-up of their cancer: seven visits will be considered for data collection over the 12-month study period, corresponding to the usual consultations with the oncologist or haematologist at the hospital. At each visit, data will be collected from the hospital clinical records, from a dedicated individual booklet filled in by the patient over time, and from the questionnaires. They will be recorded in an electronic case report form. Onsite data monitoring will be planned, and additional data quality control will be performed throughout the study.

The EQ-5D-3L will be self-administered at baseline and at each follow-up visit. This validated instrument contains five dimensions: mobility, self-care, usual activities, pain/discomfort, and anxiety/depression. Each dimension has three levels: no problems, some problems, and extreme problems.

The following resource use will be collected for costs estimation: medical consultations and laboratory and imaging examinations, performed on an outpatient basis and during hospital stay/consultations; nursing care at home; time off work; drugs taken on an outpatient basis; emergency room admissions; and hospital admissions related to OAA complications. The hospital information system of the participating centre will be used to complete hospitalisation data, as well as the French National Health Service data warehouse (ERASME) for ambulatory data.

A specific microcosting study will be carried out to estimate costs related to the implementation of the ONCORAL programme. Hence, the real time spent by the additional hospital staff required for the intervention will be counted, according to the professional category (ie, pharmacist and nurse). This will be self-reported and will relate to the preparation, realisation, and synthesis for each session; the number of actions carried out towards the community health professionals; and the different additional contacts that could take place with the patient.

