**Methods and analysis:**

This is a prospective controlled study, with individual open-label randomisation. A total of 216 outpatients treated with OAA and at risk of developing a drug-related iatrogenic event, will be randomised (2:1) to undergo follow-up in the ONCORAL programme or usual care. The primary outcome will be the estimation of the incremental cost-effectiveness ratio (difference in total costs per quality adjusted life years gained) at 12 months between the two groups. The secondary outcomes will be evaluation of OAA management consequences (relative-dose intensity, adherence, adverse drug events, drug–drug interactions, and proven medication errors), evaluation of overall survival and cancer-related quality of life, and patient-reported outcomes in relation to the treatment. A budget impact analysis will be implemented. Patient and health professional satisfaction regarding the ONCORAL programme will be measured.

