OAA, oral anticancer agent.

The allocation of patients to the two study groups will be done via a centralised online randomisation system, in an unbalanced ratio 2:1 between the ONCORAL programme and usual care. Allocation will not be blinded to participants, medical staff, nor the clinical trial staff.

During the course of the study, in the event of a change in treatment and/or complete discontinuation of OAA, the patient will be withdrawn from the study; however, its data will be considered and analysed.

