#### Primary outcome

The primary outcome will be the estimation of the incremental cost-effectiveness ratio (ICER) at 12 months between the ONCORAL programme and usual care.

The impact of OAA management monitoring will be measured using QALYs that takes into account both survival and quality of life, which is particularly relevant in cancer. The number of QALYs will be assessed using survival time and the 3-level version of the EuroQol 5 Dimensions questionnaire (EQ-5D-3L).^22^

Cost calculations will include hospital-related and ambulatory costs over the 12-month period of the study, from a French health insurance perspective and a hospital perspective.

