#### Calculation of costs

The calculation of costs will be performed over a 12-month time horizon, which does not require discounting.

From the hospital perspective, the calculation will be based on production costs (ie, gross wages plus employer’s costs and social fees) for the time spent by the staff involved in the ONCORAL programme, cost accounting data at hospital level (consultations, examinations, and emergency admissions), and the French national cost studies for hospital stays.

From the French health insurance perspective, the costing will be based on tariffs, that is, the reimbursement rates for ambulatory resources and diagnosis-related groups to estimate the cost for hospital stays. The time spent by the community pharmacists to manage patients included in the ONCORAL programme will be estimated on a sample basis and valued according to expert opinion.

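### Inpatient stays are costed only when tied to complications of the oral anticancer agent (OAA), although the primary ICER is defined on total costs and allocation is open

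*Protocol article*

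**What the plan says.** **Cost term of the primary outcome.** The Abstract (Methods and analysis) defines the ICER as the "difference in total costs per quality adjusted life years gained". The Primary outcome section gives the scope: "Cost calculations will include hospital-related and ambulatory costs over the 12-month period of the study, from a French health insurance perspective and a hospital perspective". Neither limits costs by cause.

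**Resources collected.** The Data collection section lists consultations, laboratory and imaging tests, home nursing, time off work and outpatient drugs, all without reference to cause. It then ends with "emergency room admissions; and hospital admissions related to OAA complications". The semicolon suggests that the limit applies to the inpatient item only.

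**Valuation.** For the health insurance perspective, the Calculation of costs section uses "diagnosis-related groups to estimate the cost for hospital stays". For the hospital perspective it uses national cost studies. Neither sentence repeats the limit.

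**Sources.** Information comes from clinical records, questionnaires and data "from a dedicated individual booklet filled in by the patient over time". For inpatient stays, the Data collection section adds: "The hospital information system of the participating centre will be used to complete hospitalisation data". The claims database is mentioned too, but with a different purpose: "as well as the French National Health Service data warehouse (ERASME) for ambulatory data".

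**Blinding.** The Study design and settings section states: "Allocation will not be blinded to participants, medical staff, nor the clinical trial staff". The article does not say who decides that an admission is OAA-related, by what criteria, or without knowledge of the arm.

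**The concern.** Followed as written, the cost list has three consequences for the numerator of the primary outcome.

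1. **Attribution.** A stay is costed or not according to a relatedness judgement. The eligibility table selects patients for features such as several chronic conditions, many drugs, added injectable chemotherapy and reduced renal function. In such patients, toxicity, progression and comorbidity are hard to separate. If the judgement is made with knowledge of the arm, the two arms can be costed by different standards.
2. **Mismatch within the ratio.** QALYs are built from survival time and EQ-5D-3L, neither restricted by cause. Stays for progression or comorbidity are left out of the cost even where their consequences reach the QALYs. These stays are not irrelevant to the programme: the Discussion expects it to raise relative dose intensity and says that dose intensity affects therapeutic effectiveness. It could therefore change progression-related admissions, and the costing would not show it.
3. **Stays elsewhere.** The only administrative source named for hospitalisation is the single participating centre. This matters most for the health insurance perspective, where the payer bears the cost of a stay at any hospital.

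The bootstrap and acceptability curves in the Main analyses section describe sampling uncertainty. They cannot reveal or repair an error of scope or attribution.

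**Working it through.** **Step 1: the sections side by side.**

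| Section | Inpatient scope |
|---|---|
| Abstract, Methods and analysis | total costs, no limit by cause |
| Primary outcome | hospital-related and ambulatory costs, no limit by cause |
| Data collection | admissions tied to OAA complications only |
| Calculation of costs | hospital stays, no limit by cause |

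If Data collection governs, the cost term is not total cost. If Calculation of costs governs, the Data collection list is worded wrongly. Both cannot stand.

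**Step 2: formula for the error.** The article gives no admission rates, unit costs or attribution shares, so there is no stated figure to reproduce on this point. What follows is an illustration under assumptions. Let c be the mean cost of a stay (taken as equal for related and unrelated stays), r1 and r0 the all-cause stays per patient over 12 months in the ONCORAL and usual care arms, and q1 and q0 the shares judged OAA-related.

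- Full inpatient cost difference: c × (r1 − r0)
- Costed difference: c × (r1·q1 − r0·q0)
- Error (costed minus full): c × [r0·(1 − q0) − r1·(1 − q1)]

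**Step 3: attribution alone.** Set r1 = r0 = r, so that the true difference is zero. The error becomes c × r × (q1 − q0). If the ONCORAL share is lower by d, the error is −r × d mean-stay costs per patient. If it is higher by d, the sign reverses. The assumed ranges are r = 0.5 to 1.5 and d = 0.05 to 0.20. Absolute error in mean-stay costs per patient:

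| r | d = 0.05 | d = 0.10 | d = 0.20 |
|---|---|---|---|
| 0.5 | 0.025 | 0.05 | 0.10 |
| 1.0 | 0.05 | 0.10 | 0.20 |
| 1.5 | 0.075 | 0.15 | 0.30 |

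For example, 1.0 × 0.10 = 0.10 and 1.5 × 0.20 = 0.30.

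**Step 4: scope alone.** Set q1 = q0 = q. The error becomes −c × (1 − q) × (r1 − r0): only the share q of any real difference in stays is costed. If r1 = r0, this error is zero. The number of uncosted stays per patient, r × (1 − q), runs from 0.5 × 0.4 = 0.2 (q = 0.6) to 1.5 × 0.8 = 1.2 (q = 0.2). That is a measure of how much is left out, not of bias, because an equal omission in both arms cancels in the incremental cost.

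**The case against.** The best defence is that the programme aims at drug-related harm, so OAA-related admissions follow its mechanism and avoid the noise of unrelated stays in a trial of about 215 patients that was not sized on costs. This justifies reporting those stays separately. It does not justify using them alone in a ratio defined on total costs.

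A second defence is that the article is condensed and the full protocol and supplementary table are not shown, so the list may simply be loosely worded. That may be so. The published sections would still conflict, and the correction would then be one of wording.

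Several stronger readings are tempting, and the document does not support them:

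- *That the numerator consists of OAA-attributed costs.* Only the inpatient item is clearly limited. Emergency room admissions appear to be unrestricted, as are the other listed items, and programme staff time is costed as well.
- *That stays elsewhere are certainly lost.* The centre's system serves to complete the data, and the booklet and clinical records may reveal some outside stays. The text supports a risk of under-capture.
- *That unblinded staff make the attribution, informed by the monthly programme interviews.* The article does not say who judges relatedness or on what information. Open allocation makes bias possible but does not demonstrate it.
- *That QALYs register every admission.* EQ-5D-3L is completed at baseline and follow-up visits, so a short stay between visits may leave no trace.

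**Conclusion.** The concern holds for inpatient stays. The Data collection section sets a cause limit that contradicts the total-cost definition of the primary outcome and the unrestricted wording elsewhere. With open allocation and no blinded judgement described, the limit exposes the primary cost difference to arm-dependent attribution.

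Neither size nor direction can be derived from the article. With equal true stay rates and one common mean cost per stay, the ranges assumed above give a false difference of 0.025 to 0.30 mean-stay costs per patient, in favour of either arm. With perfectly even attribution, a distortion arises only if the excluded stays truly differ between arms. A reader might take the whole omitted cost as bias; it is not, since the part common to both arms cancels. Incomplete capture of stays at other hospitals is a lesser and less certain part of the point.

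**What to change.** - Amend the Data collection list, and carry the same scope into the analysis plan, so that the main ICER costs all-cause hospital stays up to month 12. This brings it into line with the Abstract, Primary outcome and Calculation of costs sections.
- Take the stays from the centre's information system, supplemented by the booklet and clinical records. Add insurer claims for stays elsewhere if inpatient claims can be obtained; the article does not show that they can.
- Report OAA-related stays as a secondary breakdown or sensitivity analysis. State the criteria for relatedness and have it coded without knowledge of the arm, where existing records allow.

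**Cost.** The change is mostly to wording and data extraction, since the centre's system is already a planned source, and the article places the analysis plan before database freeze. Inpatient claims, if sought, may need further access. The statistical price is a larger variance of the cost difference, hence wider intervals and flatter acceptability curves.

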### Statistical considerations

#### Sample size calculation

The sample size was based on RDI, as it is associated with the effectiveness of OAA. According to the information available in the literature at the time of the study design, its value was 0.70 in usual care.^28^ We assume that the ONCORAL programme will achieve the RDI of 0.85. For an unbalanced 2:1 ratio in favour of the ONCORAL programme, a sample of 130 patients in the ONCORAL group and 65 in the usual care group will achieve a power of 80% at a 0.05 two-sided significance to detect a difference of 0.15 with a SD of 0.35. To take into account early withdrawal from the study, a total of 215 patients will be included in the study (143 in the ONCORAL group and 72 in the usual care group).

The number of patients treated with OAA in the study centre is approximately 350 per year, which will allow the recruitment of the expected number of subjects.

#### Calculation of costs

The calculation of costs will be performed over a 12-month time horizon, which does not require discounting.

From the hospital perspective, the calculation will be based on production costs (ie, gross wages plus employer’s costs and social fees) for the time spent by the staff involved in the ONCORAL programme, cost accounting data at hospital level (consultations, examinations, and emergency admissions), and the French national cost studies for hospital stays.

From the French health insurance perspective, the costing will be based on tariffs, that is, the reimbursement rates for ambulatory resources and diagnosis-related groups to estimate the cost for hospital stays. The time spent by the community pharmacists to manage patients included in the ONCORAL programme will be estimated on a sample basis and valued according to expert opinion.

#### Main analyses

The ICER will be expressed as the extra cost in euros per QALY gained following the introduction of the ONCORAL programme compared with the control group:^29^

$$ICER=\frac{C_{Oncoral}-C_{Control}}{QALY_{Oncoral}-QALY_{Control}}$$

where 
$C_{Oncoral}$
 and 
$C_{Control}$
 are the mean cost per patient in each group, and 
${QALY}_{Oncoral}$
 and 
${QALY}_{Control}$
 the mean number of QALY in each group.

The principle of calculating QALYs is to weight the time spent in health states by the preference scores associated with these states. Multiattribute health state classification systems are one of the methods of valuing health states. The EQ-5D-3L self-administered questionnaire is a multiattribute health state classification system whose preference scores are validated in France.^30^ Once the health states are described by the EQ-5D-3L, each of them is individually associated with the corresponding preference score.

A univariate sensitivity analysis will be performed to test the robustness of the cost-effectiveness analysis results and to identify the most sensitive parameters, using a Tornado diagram. The bootstrap method will be used to analyse the sampling uncertainty: 95% CIs of the parameters will be computed; and the joint uncertainty of costs and QALYs will be analysed using cost-effectiveness acceptability curves, which will represent the probability that the ONCORAL programme will be cost-effective at different willingness-to-pay thresholds.

Concerning the primary outcome, a complete case analysis, based on patients for whom all cost and effectiveness data are available, will be performed; an intention-to-treat analysis will be performed in the whole population after imputation of missing data.

Data regarding secondary outcomes will be described for each group. Missing data will be documented but there will be no imputation for secondary outcomes. A Kaplan-Meier model will be used to estimate the overall and the progression-free survival rates up to 12 months in each group, and a log-rank test will be implemented to compare them. Mixed models for repeated measures will be used to estimate the evolution of the different PROs and of cancer-related quality of life.

A pre-established statistical analysis plan will be provided prior to freezing the database and prior to conducting the analyses. All persons involved in data-management, statistical, and medico-economic analysis, as well as the principal investigator and the methodologist will have access to the final data set.

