## Methods and analysis

### Study design and settings

A prospective controlled study with individual open-label randomisation was designed to compare two groups of outpatients treated with OAA at risk of developing a drug-related iatrogenic event and benefiting from follow-up consultations by an oncologist or haematologist from the Lyon Sud Hospital of the *Hospices Civils de Lyon*, France. Patients randomised to the intervention group will benefit from the ONCORAL programme, with enhanced multidisciplinary management involving hospital and community health professionals while patients randomised to the control group will be managed according to usual care.

Each eligible participant will be recruited following the consultation for an initiation or change of OAA with a hospital oncologist or haematologist. If the patient is ambulatory, deemed to be at important risk of developing drug-related iatrogenic events with OAA, and meets all the inclusion criteria (table 1), he will be informed orally and with a detailed written notice by the investigator. Randomisation will be set up after obtaining informed consent, in accordance with the principals of good clinical practice.

**Table 1 T1:** Patient eligibility criteria

Inclusion criteria	Exclusion criteria
Adult over 18 years of age	Treatment with OAA under a clinical trial or compassionate use
Diagnosed cancer	Treatment managed at home by a caregiver exclusively
Ambulatory status (not hospitalised for the management and treatment of the cancer)	No declared attending physician
Initiation or change of OAA (indication in the context of the marketing authorisation)	No or ≥2 declared regular community pharmacies
Sufficient autonomy to manage the treatment at home*	Participation in a clinical trial that may modify the costs of care
No major psychiatric cognitive disorder likely to interfere with the ONCORAL programme*	Legal protection or institutionalisation
Considered by the oncologist to be at risk of drug-related adverse events, or to have three or more of the following risk factors for developing a drug-related adverse event:	
≥2 OAA prescribed in combination	
≥2 lines of treatment	
Combination with an injectable chemotherapy protocol	
Discontinuous OAA regimen	
≥2 associated chronic conditions	
≥5 associated drugs including OAA	
Creatinine clearance<60 mL/min	
Frailties and psychosocial conditions (isolated patient, foreigner, and limited autonomy)	

*According to the treating oncologist.

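### The primary ICER is written on arm means with no stated adjustment for baseline EQ-5D utility, which is collected; adjusting would gain precision at almost no cost

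*Protocol article*

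**What the plan says.** The Main analyses section writes the ICER as a cost difference over a QALY difference. The cost terms "are the mean cost per patient in each group, and" the QALY terms are "the mean number of QALY in each group". No regression or covariate is named for either. The work listed around the primary outcome is a one-way sensitivity analysis with a tornado diagram, a bootstrap, acceptability curves, a complete-case analysis and an intention-to-treat analysis after imputation. On the bootstrap it says that "95% CIs of the parameters will be computed".

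The Data collection section supplies the natural covariate: "The EQ-5D-3L will be self-administered at baseline and at each follow-up visit", and "seven visits will be considered for data collection over the 12-month study period". Costed resources include "drugs taken on an outpatient basis".

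Study design and settings admits any diagnosed cancer at the start or change of an oral anticancer agent (OAA). It allocates through a "centralised online randomisation system, in an unbalanced ratio 2:1 between the ONCORAL programme and usual care" and names no stratification factor. Main analyses ends by announcing a statistical analysis plan before database freeze.

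**The concern.** A patient's baseline utility enters the 12-month QALY directly and also predicts later utilities. If one arm happens to start with better utility, a difference in plain arm means carries part of that head start into the QALY difference, which is the denominator of the primary outcome. The control arm has only 72 patients, and the Discussion says that the trial could not be sized on costs or QALYs. Precision on the primary outcome was therefore never planned, and a strong predictor already in the data should not go unused.

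A related point applies to costs. Patients on many different OAAs enter, so the mix of drug prices in each arm is left to chance and passes into the cost difference wherever outpatient drugs are counted.

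**Working it through.** **The plan's own figure.** The only reproducible calculation is for relative dose intensity (Sample size calculation): difference 0.15, SD 0.35, two-sided 0.05, power 80%, ratio 2:1.

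Control n = (1.960 + 0.842)² × 0.35² × (1 + 1/2) / 0.15² = 7.85 × 0.1225 × 1.5 / 0.0225 ≈ 64.1, rounded up to 65, with 130 in the programme arm. Power at 65/130 is 0.80 to 0.81. The figure reproduces, but it says nothing about the precision of the ICER.

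**Inputs for this point.** The arm sizes of 143 and 72 are from Sample size calculation. The rest are assumptions, because the documents give no values: SD of baseline utility 0.15 to 0.30; slope of 12-month QALY on baseline utility 0.4 to 0.8; baseline-QALY correlation ρ 0.3 to 0.7.

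**Chance imbalance.** SE of the baseline difference = SD × √(1/143 + 1/72) = SD × 0.1445. The shift in the unadjusted QALY difference is slope × imbalance.

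| Assumed SD | SE of baseline difference | 95% range | P(gap above 0.03, either direction) | QALY shift at a 1.96-SE gap, slope 0.4 to 0.8 |
|---|---|---|---|---|
| 0.15 | 0.022 | ±0.042 | 0.17 | 0.017 to 0.034 |
| 0.20 | 0.029 | ±0.057 | 0.30 | 0.023 to 0.045 |
| 0.25 | 0.036 | ±0.071 | 0.41 | 0.028 to 0.057 |
| 0.30 | 0.043 | ±0.085 | 0.49 | 0.034 to 0.068 |

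The last column is an unlucky draw, not a typical one. The expected absolute gap is SE × √(2/π). At SD 0.25 this is 0.036 × 0.798 = 0.029, and the typical QALY shift is 0.029 × 0.4 to 0.8 = 0.012 to 0.023.

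**Route of carry-over.** With trapezoidal QALYs, the baseline score itself has a weight of half the first interval. If the second visit is at 1 month that is 1/24 = 0.042 year; if at 2 months, 2/24 = 0.083 year. (Both schedules are assumed; the visit times are in a supplement not shown.) Most of the carry-over therefore comes from correlation with later utilities.

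**Gain from adjustment.** Variance ratio = 1 − ρ².

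| ρ | Variance remaining | SE remaining | Unadjusted N giving the same precision as 215 adjusted |
|---|---|---|---|
| 0.3 | 0.91 | 95% | 215/0.91 ≈ 236 |
| 0.5 | 0.75 | 87% | 215/0.75 ≈ 287 |
| 0.6 | 0.64 | 80% | 215/0.64 ≈ 336 |
| 0.7 | 0.51 | 71% | 215/0.51 ≈ 422 |

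**Costs.** The effect of OAA mix cannot be computed, because the documents give neither drug prices nor the distribution of agents. It also does not reach both perspectives. In Calculation of costs, the hospital-perspective items are staff time, consultations, examinations, emergency admissions and stays. Outpatient drugs are not among them, and the Usual care section has OAAs dispensed by community pharmacists.

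**Why an ICER interval would need care.** Suppose the SE of the QALY difference is 0.036 (assumed QALY SD 0.25) and the true gain is 0.02, 0.03 or 0.05 (also assumed). The chance of a negative QALY difference is then Φ(−0.56) = 0.29, Φ(−0.83) = 0.20 or Φ(−1.39) = 0.08. Once the denominator can change sign, a negative ratio can mean either dominant or dominated.

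**The case against.** The strongest reply is that the formula is the generic definition of an ICER. It does not describe the means as raw or unadjusted, and regression-adjusted arm means fit it equally well. A statistical analysis plan is announced, and covariate adjustment is often settled there. This stands in part: nobody can conclude from the article that no adjustment will be made. What remains is that the article defines the terms of its primary estimator, lists the supporting analyses without an adjusted one, and names mixed models for other outcomes in the same section. The natural reading is a comparison of plain means, and a better estimator is available from data already collected.

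A reader might go further and infer that chance imbalance biases the result. It does not. Allocation is central and individual, so imbalance adds variance, and the planned bootstrap and acceptability curves already carry that variance. The loss is in precision and in accuracy for the sample actually drawn.

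A reader might also infer that a typical imbalance is as large as a plausible programme effect. That requires baseline differences to pass one-for-one into QALYs; with slopes of 0.4 to 0.8 the typical shift is smaller, and the documents state no expected QALY gain to compare it with.

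Finally, a reader might infer that the plan commits to a percentile interval for the ICER. The text neither says percentile nor lists the ICER among the parameters. It assigns the joint uncertainty of costs and QALYs to acceptability curves, which is a sound method.

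**Conclusion.** The point holds as a matter of efficiency. Read as written, the primary QALY contrast is valid under randomisation but less precise than it need be, and exposed to chance baseline imbalance. Under the assumed ranges, the SE of the baseline difference is 0.022 to 0.043, and adjustment would cut the variance of the QALY difference by about 9% to 49%. These sizes rest on an assumed utility SD and correlation, not on trial data. The cost limb is weaker: it concerns only the health insurance perspective and cannot be quantified. The concern about an interval for the ICER is conditional on what the bootstrap sentence is meant to cover. If the unseen analysis plan already adjusts for baseline utility, only confirmation is needed.

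**What to change.** Before database freeze, state in the analysis plan:

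- Incremental QALYs are estimated by linear regression on arm and baseline EQ-5D-3L utility, in both the complete-case and the imputed analyses.
- Patients are resampled within arm, with costs and QALYs kept together and the model refitted in each resample. The ICER and acceptability curves are built from the adjusted QALY difference.
- Unadjusted means are reported as a sensitivity analysis.
- Optionally, for the health insurance perspective, incremental costs are adjusted for the OAA at inclusion.
- If the bootstrap intervals are meant to include the ICER, intervals for incremental cost, incremental QALYs and net monetary benefit at stated thresholds are reported instead.

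The cost is a few sentences and a few lines of code, with no new data for the QALY model. Timing matters: allocation is open, so an adjustment chosen after results are seen could be challenged.
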